### **7.3 Demographics and Baseline Characteristics**

All data recorded at baseline will be summarized by group. Comparisons between groups will be done using the methodology described in section 7.1.

### **7.4 Analyses for Outcomes**

The analysis of proportion of participants with at least 20% reduction from baseline in the amount of methadone dose is performed using a generalized linear mixed model. For opioid craving VAS and all secondary outcomes, analysis is conducted utilizing a

linear mixed-model. For above models, values measured at baseline are used as covariates; intervention assignment, visit and intervention  $\times$  visit interaction are as fixed effects; and treatment centre and centre  $\times$  intervention interaction are as random effects. Before building the final model, we assess the poolability of treatment effects across centres by including centre  $\times$  intervention interaction in the model. If *P*-values corresponding to the interaction term for both primary endpoints are greater than 0.10, the treatment effect is homogenous across centres and centre  $\times$  intervention interaction will not be included in the final model. Primary outcomes use 2-sided tests at the 2.5% significance level. All other statistical tests are 2-sided at the 5% significance level. Dynamic data on the reduction in the methadone consumption and the opioid craving VAS score will be demonstrated in the figures, separated by two groups. Each row in the figures represents the reduction dose of the daily consumption of methadone (the opioid craving VAS score) for one participant. To investigate the relationship between daily consumption of methadone and the intensity of opioid craving over a 20-week period, scatter plots will be employed as a visual representation in this study with the x-axis representing the opioid craving VAS and the y-axis representing the methadone dose. The resulting scatter plot allows for the examination of the correlation between these two variables, providing insights into the potential influence of methadone intake on opioid craving levels over time.

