Our group has previously conducted a clinical trial and literature review to initially explore the potential of acupuncture in reducing the daily consumption of methadone and opioid cravings in MMT clients. Our RCT demonstrated that acupuncture surpasses standalone methadone therapy in reducing methadone dosage, improving drug cravings, and addressing insomnia without concomitantly increasing the rate of positive urine tests for opioids [40]. Meanwhile we also assessed the economic value of acupuncture from a health economics perspective in this trial [41]. Another study conducted a comprehensive and systematic evaluation of acupuncture and non-pharmacological therapies for improving drug dependence and addressing

neurological symptoms, revealing the potential of acupuncture to alleviate withdrawal symptoms and enhance neurological function among individuals with substance dependence [42,43].

In general, although there have been several studies focusing on acupuncture as an adjunct treatment for drug addiction, they have predominantly consisted of small-sample clinical trials without the inclusion of sham acupuncture as a control. Consequently, there is a compelling need to undertake high-quality prospective RCT incorporating sham acupuncture as a control in order to substantiate and affirm the efficacy and safety of acupuncture in MMT, thereby providing more persuasive evidence.

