## **7. Urine Test**

All participants will be asked to submit a urine sample at baseline, and randomly during the study each month, which are used to test for opioid use.

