## 11. Statistical Analysis

Statistical analysis will be performed by the Clinical Research and Big Data Laboratory, South China Research Center for Acupuncture and Moxibustion, Guangzhou University of Chinese Medicine. The statistician will be blinded to group allocation until final unblinding. SAS 9.4 will be utilized for data analysis. Missing data are filled by using multiple imputation.

Continuous variables are reported as the mean with standard deviation or median and interquartile range. Categorical variables are described as numbers and percentages using  $\chi^2$  test or Fisher's exact test. Longitudinal measures through 20 weeks (8 weeks of intervention and 12 weeks of follow-up) are analyzed for all outcomes. The analysis of proportion of participants with at least 20% reduction from baseline in the amount of methadone dose is performed using a generalized linear mixed-model. For opioid craving VAS and all secondary outcomes, analysis is conducted utilizing a linear mixed-model. For above models, values measured at baseline are used as covariates; intervention assignment, visit and intervention  $\times$  visit interaction are as fixed effects; and treatment centre and centre  $\times$  intervention interaction are as random effects. We assessed the poolability of treatment effects across centres by including centre  $\times$  intervention interaction in the model. If *P*-values corresponding to the centre  $\times$  intervention interaction term for both primary endpoints are greater than 0.10, the treatment effect is homogenous across centres [59].

Dynamic data will be demonstrated on the reduction in the methadone consumption and the opioid craving VAS score in the figures, separated by the manual acupuncture and sham group. Each row in the figures represents the reduction dose of

the daily consumption of methadone (the opioid craving VAS score) for one participant. Individuals who discontinue participation early appear at the bottom of each plot, whereas those with complete data appear at the top.

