## **7. Statistical Analysis**

### **7.1 Summary Statistics**

Continuous variables are reported as the mean with standard deviation or median and interquartile range. Categorical variables are described as numbers and percentages. Continuous variables will be compared using a two-sample t-test or Wilcoxon rank-sum test if data show serious deviations from a normal distribution. Categorical data or ordinal data will be compared using a Wilcoxon rank-sum test, chi-square test or Fisher's exact test, as appropriate.

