### **7.2 Missing Data**

We will use multiple imputation method under the missing at random (MAR) assumption for the primary and secondary outcome with missing data. Multiple imputations use the observed data to fill in the missing values repeatedly to give rise to multiple "pseudo-complete" datasets. We will perform the imputation of missing data 100 times using regression imputation, employing the SAS procedure Proc MI process. For each time point, measurements of primary and secondary outcomes are imputed using groups, baseline measurements, and measurements prior to the time point as covariates in regression models. The estimated values are set as integers, and 100 different datasets are generated. By calculating the median of all estimated values for missing data, the 100 imputed datasets are merged into one.

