### **7.8 Analysis Software**

Statistical analyses are conducted by an independent statistician using SAS version 9.4 (SAS Institute Inc, Cary, NC), including SAS PROC GLIMMIX for generalized linear mixed model, and SAS PROC MIXED for linear mixed-model.

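### SAP 5.2 and 7.4, read literally, put the urine opioid test into a linear mixed model, and SAP 7.2 forces each missing urine result to its more likely category

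*Combined protocol and SAP*

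**What the plan says.** SAP 5.2 names five secondary outcomes: COWS, PSQI, BDI-II, BAI and the urine test. The first four are summed scores. Protocol section 6.2 names only those four. It describes the urine test separately in section 7: one sample at baseline, then samples taken "randomly during the study each month, which are used to test for opioid use".

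SAP 7.4 gives the outcome models. The proportion with at least a 20% dose reduction "in the amount of methadone dose is performed using a generalized linear mixed model". For the rest, "For opioid craving VAS and all secondary outcomes, analysis is conducted utilizing a" linear mixed model. SAP 7.8 confirms the split, "including SAS PROC GLIMMIX for generalized linear mixed model, and SAS PROC MIXED for linear mixed-model". Nothing in the SAP exempts the urine test.

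SAP 7.1, under summary statistics, has a general rule: "Categorical data or ordinal data will be compared using a Wilcoxon rank-sum test, chi-square test" or Fisher's exact test. It does not mention urine.

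On missing values, SAP 7.2 states: "We will use multiple imputation method under the missing at random (MAR) assumption for the primary and secondary outcome with missing data". Group, baseline and earlier measurements are the predictors. Imputed values are made integers, 100 datasets are produced, and each missing value is replaced by the median of its 100 estimates to give one dataset.

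**The concern.** Neither document says how a urine result is coded. Positive or negative is the natural reading: the samples test for opioid use, and the background section reports the group's earlier trial as reducing methadone "without concomitantly increasing the rate of positive urine tests for opioids". On that reading the SAP has two binary outcomes. It uses a generalized model for one and a normal-error model for the other.

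The imputation rule adds a second problem. The median of many rounded draws is not a draw from the predictive distribution. For a 0/1 result it amounts to a cut at a predicted probability of one half, and the filled-in value is then analysed as if it had been observed.

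The urine test is the trial's only laboratory check on whether a lower methadone dose is accompanied by other opioid use. SAP 7.5 confines sensitivity analysis to the primary outcomes, so nothing planned would show how far the urine comparison depends on the filled-in values.

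**Working it through.** **Which rule applies to urine**

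| Question | Protocol | SAP |
|---|---|---|
| Secondary outcome? | No: section 7, outside 6.2 | Yes: 5.2 |
| Model | None named | Linear mixed model through 7.4; 7.1 has a generic categorical test |
| Imputed? | Multiple imputation, outcomes not listed | Yes: 7.2 covers secondary outcomes |
| Timing | Baseline, then at random each month | Not in the assessment schedule; the model uses visits |

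**What the integer-and-median rule does**

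The documents give no positivity rate, missing rate or power for urine, so there is no figure to reproduce. The check is of the mechanism. Let p be the predicted probability that a missing result is positive, with m = 100 imputations (SAP 7.2). SAP 7.2 does not say which kind of regression is used, so two forms were taken.

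(a) Linear regression draws from a normal distribution with mean p and variance p(1 − p), rounded to integers. The chance that one draw rounds to 1 or more is q = 1 − Φ[(0.5 − p)/√(p(1 − p))]. The merged value is 0 when at most 49 of the 100 draws do so: P(0) = P[Bin(100, q) ≤ 49].

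(b) Draws of 0 or 1 with probability p: P(0) = P[Bin(100, p) ≤ 49].

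Example for (a) at p = 0.40: (0.5 − 0.4)/√0.24 = 0.204, so q = 0.419 and P(0) = 0.937. A simulation with 20,000 repeats gave 0.935.

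| p | P(merged value is 0), (a) | P(merged value is 0), (b) |
|---|---|---|
| 0.10 | 1.000 | 1.000 |
| 0.20 | 1.000 | 1.000 |
| 0.30 | over 0.999 | over 0.999 |
| 0.40 | 0.937 | 0.973 |
| 0.45 | 0.759 | 0.817 |
| 0.50 | 0.460 | 0.460 |
| 0.60 | 0.042 | 0.017 |
| 0.70 | under 0.001 | under 0.001 |

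At p = 0.50 about 8% of merged values are 0.5, which is not a possible result.

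**Which participants fall on each side of one half**

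Earlier results are predictors, so p differs between participants. As an illustration, assume a mean positivity of 20% and a within-person correlation of 0.4 (beta-binomial). Then s = 1/0.4 − 1 = 1.5, a = 0.20 × 1.5 = 0.30, and after k positives in 3 samples p = (0.30 + k)/(1.5 + 3):

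- k = 0: 0.07
- k = 1: 0.29
- k = 2: 0.51
- k = 3: 0.73

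Participants with no or one earlier positive are filled in as negative. Those with three are filled in as positive. Those with two are close to a coin toss.

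**Size of the bias in the rate**

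Assume 15% of samples are missing (the planning attrition in protocol section 10, borrowed for illustration), that missing and tested samples have the same positivity r, and that every missing one is scored negative. The reported rate is 0.85 × r:

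- r = 10%: 8.5%
- r = 20%: 17%
- r = 30%: 25.5%
- r = 40%: 34%

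With these assumptions in both arms, the risk difference shrinks by the same factor of 0.85. Any missing results filled in as positive would make the shortfall smaller.

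**The case against.** The strongest reply is that the SAP is ambiguous rather than committed to a linear model, since SAP 7.1 offers chi-square or Fisher tests for categorical data. That stands in part. But 7.1 concerns summary statistics and does not name urine, while 7.4 is the section on outcome analyses and covers all secondary outcomes. A single chi-square test would also not handle repeated monthly samples. Two readings of a pre-specified analysis still need to be reduced to one.

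It can also be said that the protocol does not have this problem, and that is right. Protocol section 11 has the sentence "For opioid craving VAS and all secondary outcomes, analysis is conducted utilizing a linear mixed-model", but the protocol's secondary outcomes exclude urine, so it should not be read as sending urine to that model. The difficulty comes from the SAP's list.

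A linear model on 0/1 data does estimate a risk difference, for which negative limits are legitimate. A reader might point to a normal-theory interval for one arm, such as −1% to 11% at 5% positive with 50 participants, as proof that the comparison is unreliable. That interval is for a single proportion, not the treatment contrast, and proves nothing about it.

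Monthly sampling is not incompatible with a repeated-measures model either: samples can be indexed by study month. The SAP simply does not say so. Lastly, integer-and-median merging is a general feature of SAP 7.2 and not specific to urine. This is true, but its effect on a 0/1 outcome is especially blunt.

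**Conclusion.** The point holds, as a matter of SAP wording that would be wrong if followed. A result that is by inference positive/negative is sent to a normal-error model, and each missing value is forced to its likelier category with its uncertainty discarded. If positives are uncommon, most missing samples would be scored negative. In the illustration a rate of 20% is reported as 17%, a loss of 3 percentage points, even under missing at random. The 20%, the 15% and the scoring of every missing sample as negative are assumptions.

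Two stronger readings are not supported. A reader might infer that missing samples are always scored negative. SAP 7.2 does not say so, the merged value is 0 only about 76% of the time at a predicted 45%, and participants predicted well above 50% are scored positive. A reader might also set the 17% against a true rate of 24.5% (0.85 × 20% + 0.15 × 50%). That adds an assumed 50% positivity among the missing, which departs from missing at random. The extra 4.5 points would not be removed by any imputation under that assumption, and the documents give no basis for the 50%.

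**What to change.** 1. Reconcile the status of the urine test between protocol section 7 and SAP 5.2, and state how a result is coded.
2. In SAP 7.4, take urine out of the linear mixed model. Analyse positive/negative by study month with a logistic mixed model in PROC GLIMMIX, with a participant random intercept and the baseline result as covariate, and report the risk difference with its interval. Say how a randomly timed sample is assigned to a study month.
3. In SAP 7.2, replace integer-and-median merging for urine with logistic multiple imputation, analysing each dataset and pooling by Rubin's rules.
4. Add a sensitivity analysis that counts missing samples as positive. This addresses departures from missing at random, which step 3 alone does not.

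The cost is revised SAP text and a little more analysis work. PROC GLIMMIX is already planned for the methadone outcome, and no new data are needed.

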#### **6.1.2 Opioids Craving Visual Analog Scale**

The other primary outcome is the opioid craving using a visual analog scale for drug craving marking on a 100-millimetre line in proportion to their craving from 0 (no craving) to 100 (strong craving)[50]. The degree of craving will be marked by subjects at baseline, the 2nd, the 4th, the 6th, and the 8th week after acupuncture administration and at the post-treatment follow-up visits in the 12th, the 16th, and the 20th week. The minimal clinically important difference (MCID) for the opioid craving VAS is 4.0 points [51,52].

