### **6.2.2 Pittsburgh Sleep Quality Index (PSQI)**

Sleep quality will be assessed using the Chinese version of the PSQI[54] from baseline to the 4th, the 8th, the 12th, the 16th and the 20th week. The Chinese version of PSQI has demonstrated reliability and validity similar to that of the original language version [55]. PSQI evaluates sleep disturbances through subjective sleep quality, sleep duration, sleep latency, habitual sleep efficiency, sleep disturbances, daytime dysfunction and use of sleeping medication. Each item is graded on 4-point (0–3), which is summed together and gains a total score (0 to 21). Higher scores show that patients suffer severity of sleep disturbance and a total score higher than 5 indicates “poor sleep”.

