## **5. Efficacy and Safety Outcomes**

### **5.1 Primary Outcomes**

One primary outcome is the rate of methadone dose reduction, defined as the proportion of participants who achieve a reduction in methadone dose of  $\geq 20\%$  compared to baseline after 8 weeks of intervention. The other primary outcome is the opioid craving using a visual analog scale for drug craving marking on a 100-millimetre line in proportion to their craving from 0 (no craving) to 100 (strong craving)

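### The repeated-measures models name no participant-level term and no tested contrast, so the error rate of the primary tests depends on choices the plan leaves open

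*Combined protocol and SAP*

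**What the plan says.** Protocol section 11 states: "Longitudinal measures through 20 weeks (8 weeks of intervention and 12 weeks of follow-up) are analyzed for all outcomes". It and SAP 7.4 then give the same model. On the fixed side: "values measured at baseline are used as covariates; intervention assignment, visit and intervention" by visit. On the random side there are two terms, treatment centre and its interaction with treatment: centre by "intervention interaction are as random effects".

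SAP 7.4 adds a model-selection step: "Before building the final model, we assess the poolability of treatment effects across centres by including centre" by intervention. If P exceeds 0.10 for both primary endpoints, that interaction is left out of the final model. Primary outcomes are tested two-sided at 2.5%, all others at 5%.

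SAP 7.8 names PROC GLIMMIX for the binary outcome and "SAS PROC MIXED for linear mixed-model", with no subject, covariance structure or degrees-of-freedom method.

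The dose outcome is defined "compared to baseline after 8 weeks of intervention" (SAP 5.1). For the craving VAS, protocol section 6.1.2 lists the assessment weeks and SAP 5.1 describes the scale; neither picks a primary week.

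**The concern.** A patient's craving scores at weeks 2, 4, 6, 8, 12, 16 and 20 will be correlated, and so will the dose-response indicators. Neither SAS procedure adds a within-patient term by default. A programmer who codes exactly the listed effects will therefore analyse up to 100 × 7 = 700 rows as if only centre linked them.

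Two things are then at risk. The standard error of any effect averaged over visits is too small. The poolability check also misreads ordinary patient-to-patient variation as variation in the treatment effect between centres, so the rule that selects the final model does not do what it is meant to do. Both primary outcomes go through this model and this rule.

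**Working it through.** **Inputs from the documents.** Protocol section 10 needs 42 per group and allows 15% attrition: 42/0.85 = 49.4, so 50 per group, as stated. There are seven post-baseline visits for VAS, COWS and dose, and five for PSQI, BDI-II and BAI (protocol sections 6 and 9). Alpha is 2.5% two-sided for the primary outcomes and 5% for the rest.

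**Assumptions.** The available text gives neither the visit correlation nor the number of centres. I take equal correlation between all visits (ρ = 0.3 to 0.7), equal variances, 3 to 8 centres unless noted, no missing data and no true centre effects. The plan states no error rate for these models, so there is no figure to reproduce.

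**Step 1: visit-averaged test, interaction dropped.** With V visits and residual correlation r, the true variance of a patient's mean is σ²[1+(V−1)r]/V; the listed model uses σ²/V. The design effect is DE = 1+(V−1)r, and the true error is 2[1−Φ(z/√DE)], with z = 2.241 at 2.5%. Adjusting for baseline lowers the residual correlation to r = (ρ−ρ²)/(1−ρ²) = ρ/(1+ρ).

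| ρ | r after baseline | DE (7 visits) | z/√DE | True error |
|---|---|---|---|---|
| 0.3 | 0.231 | 2.385 | 1.451 | 14.7% |
| 0.5 | 0.333 | 3.000 | 1.294 | 19.6% |
| 0.7 | 0.412 | 3.471 | 1.203 | 22.9% |

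Null simulation of the baseline-adjusted model gives 14-26% over the same range. If the residual correlation itself, after baseline adjustment, is 0.3, 0.5 or 0.7, DE is 2.8, 4.0 or 5.2 and the error is 18%, 26% or 33%. For five visits at 5% (z = 1.960) the same residual correlations give DE 2.2, 3.0 and 3.8 and errors of 19%, 26% and 31%. A simplified simulation of the binary outcome, treating visits as independent, gave 13%, 19% and 25% at latent correlations of 0.3, 0.5 and 0.7.

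**Step 2: poolability check.** Approximated as a fixed-effect F test, its statistic is inflated by about DE. With 3 centres (2 numerator df) the chance of P ≤ 0.10 under the null is close to 0.10^(1/DE): 0.10^(1/2.385) = 38% at ρ = 0.3 and 0.10^(1/3.471) = 52% at ρ = 0.7. Simulation over 3, 5 and 8 centres gives 39-87%, against a nominal 10%.

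**Step 3: interaction kept.** The random interaction absorbs the unmodelled patient variation. In simulation with 3, 5 and 10 centres, tested on centre-level degrees of freedom, the intervention test rejects in 0-2.4% of null trials. It is not liberal, but power can fall.

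**Step 4: week-8 contrast.** This uses one row per patient, so within-patient correlation hardly enters. Simulated error is 2.3-3.1% for the VAS and 2.3-2.5% for the binary outcome.

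**Step 5: the remedy.** With the patient as the unit of analysis, the visit-averaged test returns to 2.5-2.8%.

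**The case against.** The strongest reply is that the plan is silent, not wrong. A residual covariance is not a random effect, so a list of random effects does not exclude one. The data are called longitudinal, and the procedures named can model the correlation. That stands in part. A reader might infer that the plan declares visits independent; no sentence says so. But the model is otherwise written out term by term in both documents, and nothing elsewhere supplies the missing piece.

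A reader might also infer that the intervention test is badly anti-conservative whatever is done. The documents do not support that. The dose outcome is tied to week 8, the model contains the intervention-by-visit term needed to extract that contrast, and the contrast is close to nominal. The overall intervention-by-visit test, simulated without baseline adjustment, becomes conservative (0-0.8% at a nominal 5%). Nor is 14-26% the error of the whole two-stage procedure: rejections reached after dropping the interaction make up about 4-11% of all null trials, because the faulty check often keeps the term.

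Finally, a specific power loss might be inferred for the branch that keeps the interaction. For the dose outcome, a test on centres-minus-one degrees of freedom gives 26%, 52% or 68% with 3, 5 or 8 centres and 42 per arm, but 29%, 60% or 76% with 50 per arm. The plan states no degrees-of-freedom method and the centre count is assumed, so these figures cannot be attributed to the trial.

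What survives is that SAP 7.4 does not name the tested contrast and the VAS has no primary timepoint. The reassuring reading is available but not prespecified.

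**Conclusion.** The omission is real, appears in both documents and should be corrected before unblinding. Its consequence depends on contrast and branch. A visit-averaged primary test with the interaction dropped would run at roughly 14-26% instead of 2.5%, or up to about 33% if the residual correlation after baseline adjustment is 0.7. The poolability check would fail in roughly 40-87% of trials with no heterogeneity. A week-8 contrast would be essentially sound, and a retained interaction would cost power, not validity. Since the plan does not fix the contrast, the error rate of the co-primary VAS test is undetermined. The sizes rest on the assumed correlation, centre count and equal-correlation structure, and the poolability figure also on the fixed-effect approximation. The absence of a participant-level term does not rest on any assumption.

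**What to change.** In SAP 7.4 and protocol section 11:

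- **Linear model.** State the within-participant covariance, for example REPEATED visit / SUBJECT=participant with an unstructured matrix and Kenward-Roger degrees of freedom in PROC MIXED. Seven visits mean 7 × 8/2 = 28 covariance parameters, so name a fallback structure in case of non-convergence.
- **Generalized model.** State either a participant random intercept or an R-side structure in PROC GLIMMIX. Choose in advance, because the first estimates a participant-specific odds ratio and the second a marginal one.
- **Contrast.** Name the week-8 treatment difference as the primary contrast for the dose outcome, as its definition already implies, and state one primary timepoint for the VAS.
- **Centre check.** Run the centre-by-intervention check only in the model that contains the participant-level term.

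The cost is a few sentences in the SAP and a few lines of code, with no new data. Standard errors for visit-averaged effects will be larger, and correct.
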